**Results:**

We expect to find that for patients with early endometrial cancer, the 3-year disease-free survival rate following sentinel lymph node biopsy with indocyanine green combined with near-infrared fluorescence imaging is similar to that following lymphadenectomy. The operation time, as well as incidence of pelvic lymphocyst, lymphedema of lower limb, and edema of vulva in patients who only undergo sentinel lymph node biopsy are expected to be significantly lower than in patients who undergo lymphadenectomy. The quality of life of patients who undergo sentinel lymph node biopsy alone will be significantly better than that of patients who undergo lymph node dissection.

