### Statistical methods

Disease-free survival and overall survival curves will be evaluated using the Kaplan Meier method. The survival difference between the two groups will be analyzed by log-rank method. The analysis of prognostic factors will use appropriate regression models (such as Cox model). Efficacy indicators will be compared through intention-to-treat analysis including all randomized patients. Toxicity will be analyzed based on the treatment received. The 95% confidence interval of the difference between the two groups will be calculated at the same time. Descriptive statistical analysis will be used for treatment-related adverse events and quality of life scores (QLQ-C30, QLQ-CX24). The normality and equality of differences between the two groups of continuous variables will be evaluated. Discrete variables (such as presence/absence of postoperative infection) will be aggregated by frequency/proportion.

For continuous variables, analysis of variance and/or regression analysis will be used as appropriate. If the assumptions of these tests are violated, an alternative nonparametric test method will be used. Differences in discrete variables between groups will be assessed by chi square test. The risk proportional regression model will be used to explore the prognostic factors such as age, degree of differentiation, lymph node metastasis, and PS-ECOG.

The hypothesis H0: “Sentinel lymph node biopsy alone is not inferior to sentinel lymph node biopsy plus lymphadenectomy for early stage endometrial cancer with negative nodal assessment intraoperatively.”

In the current study, there are three patient groups: intention-to-treat (ITT) group, including all randomized patients who signed the consent form; a group of those in serious violation of the protocol, excluded from the efficacy analysis; and a safe population of all randomized patients who at least start the study treatment.

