**Chest X-ray or Chest CT**						
**Upper abdominal CT**	x					x^c^
**Pelvic MRI**	x					x^c^
**Endometrial diagnostic curettage pathology**	x					
**Surgery approach (laparoscopic or robotic)**		x				
**SLN mapping and biopsy**		Arm A & B				
**Histological examination**		x				
**TH + BSO**		x				
**PLN dissection**				Arm B		
**paraaortic lymph node resection**		x^a^		x^a^		
**Adverse Events (CTCAE V3.0)**					x	x
**Questionnaires (EORTC QLQC30; EORTC QLQ-CX24)**	x					x

*ECG* Electrocardiogram, *PS-ECOG* Performance Status-Eastern Cooperative Oncology Group, *CT* Computed Tomography, *MRI* Magnetic Resonance Imaging

^a^ See “Additional instructions” from “Operation procedures” section

^b^ If necessary

^c^ Upper abdominal CT and pelvic MRI will be done 6 months after the initial treatment, and if necessary within three years

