#### Postoperative investigation

The following interviews are planned at 1 month, then every 3 months after surgery for 3 years:

Complete the quality of life assessment form (QLQ-C30, QLQ-CX24);Review PS-ECOG;Physical exam and pelvic examination, tumor assessment (if necessary)Record the whole blood cell count and biochemical indexesAdverse event assessment (Common Terminology Criteria for Adverse Events (CTCAE) V3.0);Postoperative pelvic B-ultrasound is used to determine whether there is a lymphocyst. If the patient has symptoms such as swelling and pain in the lower extremities, color Doppler ultrasound in the lower extremities will be used to assess the presence or absence of DVT. The development of lymphedema is investigated and evaluated by measuring the circumference of the legs and combining with the methods of pelvic ultrasound.

In addition, upper abdominal CT and pelvic MRI will be done 6 months after the initial treatment, and if necessary within three years.

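### Quality of life: the questionnaire schedule contradicts itself at 30 days, and the analysis named for the scores does not clearly support the significant advantage that the abstract expects

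*Protocol article*

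**What the plan says.** **Collection.** Under Preoperative investigation, patients complete a quality-of-life assessment before surgery, so a baseline score exists. Postoperative investigation then states: "The following interviews are planned at 1 month, then every 3 months after surgery for 3 years". The first item listed for those visits is the QLQ-C30/QLQ-CX24 form. Table 1 (Visit procedures) has separate columns for a 30-day postoperative visit and for the three-monthly follow-up visits. Its row "Questionnaires (EORTC QLQC30; EORTC QLQ-CX24" is marked at inclusion and at follow-up, and is blank at 30 days.

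**Analysis.** Outcomes lists quality of life as a secondary endpoint. The one sentence in Statistical methods that names it reads "Descriptive statistical analysis will be used for treatment-related adverse events and quality of life scores". The same section also carries general rules that name no endpoint: "For continuous variables, analysis of variance and/or regression analysis will be used as appropriate", then "If the assumptions of these tests are violated, an alternative nonparametric test method will be used", and, a little earlier, "The 95% confidence interval of the difference between the two groups will be calculated at the same time".

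**Intended claim.** The abstract's Methods section says that the two groups will be compared on quality of life. Its Results section expects that quality of life after "sentinel lymph node biopsy alone will be significantly better than that of patients who undergo lymph node dissection". Its Conclusion expects better quality of life, without the word for significance.

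**The concern.** Two pairs of statements cannot both be followed as they stand.

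On collection, a site working from the table would not hand out the questionnaire at the 30-day visit, and a site working from the text would. The 30-day score is the first after surgery, and a patient-reported score that was not collected cannot be reconstructed later. If sites differ, the early time point is also missing by centre.

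On analysis, a descriptive summary gives no basis for a statement of statistical significance. If the specific sentence governs, the expected result cannot be delivered. If the general rules govern instead, the article does not say so, and it is left open which of two multi-scale instruments and which of many visits would carry the claim. That latitude matters more here because the trial is open-label and the outcome is reported by patients who know their allocation.

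**Working it through.** The plan gives no sample-size or power figure for quality of life, so there is no stated number to reproduce. The check is mainly a comparison of texts.

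**1. Number of post-operative questionnaires**

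- Text (Postoperative investigation): one at 1 month, plus one every 3 months over 36 months, read as months 3, 6, …, 36. 1 + 36/3 = 1 + 12 = 13.
- Table 1: none at 30 days, plus the three-monthly visits of years 1 to 3. 0 + 12 = 12.
- Difference: 1 of 13 per patient. With 722 patients planned, between 0 (every site follows the text) and 722 × 1 = 722 (every site follows the table) 30-day assessments would be absent. The article does not show where in that range the trial lies.

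**2. Is the blank cell an artefact of text extraction?** Three rows were split into their cells. Each has seven: a label and six columns.

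| Row | Inclusion | 30-day visit | Follow-up |
|---|---|---|---|
| Physical exam | x | x | x |
| Adverse events | blank | x | x |
| Questionnaires | x | blank | x |

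The questionnaire row has as many cells as the other two, and its two marks sit in the right columns. Gynecological examination, performance status and blood tests are also marked at 30 days. A lost mark is unlikely.

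**3. What analysis is planned for the scores?**

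- The specific sentence assigns descriptive analysis. It does not say that nothing else will be done.
- The general rule gives analysis of variance or regression for continuous variables, with a nonparametric fallback. It neither names nor excludes the questionnaire scores.
- The confidence-interval sentence names no endpoint.
- The descriptive sentence also covers adverse events. Yet postoperative infection is the section's own example of a discrete variable, and discrete variables get a chi-square test. So in this section the word descriptive need not rule out a test.
- The abstract plans a comparison and expects significance.

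Both readings survive: described without a test, or tested under the general rule. The text does not settle which.

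**4. Would one pre-specified comparison be feasible?** For a simple two-arm comparison of means at two-sided 0.05 and 80% power, the detectable difference in standard deviations is (1.96 + 0.842) × √(2/n).

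- n = 361 per arm: 2.802 × √(2/361) = 0.21.
- n = 289 per arm, after the planned 20% loss (361 × 0.8 = 288.8): 2.802 × √(2/289) = 0.23.

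The planned size is therefore no obstacle to a single named contrast. This step bears on the remedy and is not evidence of the defect.

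**The case against.** The strongest case against the analysis half is that the article condenses a fuller protocol, and that the general rule for continuous variables naturally takes in questionnaire scores. On that view the abstract merely voices an expectation and states no hypothesis, and the choice of scale, time window, model and covariates belongs in the analysis plan. Most of this stands. The absence of that detail is not an error, and the point does not rest on it. What remains is that the one sentence naming the endpoint points one way and the abstract another.

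Three stronger readings are tempting, and the documents do not support them:

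- A reader might infer that quality of life will be analysed descriptively and in no other way. The text contains no such restriction, and the general rule could apply.
- A reader might infer that the baseline score goes unused. No sentence says so, and regression where appropriate could include it.
- A reader might attach a false-positive rate to testing at all 13 visits. The article proposes no such series of tests, and repeated scores in the same patients are not independent. Such a figure would not measure an error in this document.

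Against the schedule half, Table 1 is imperfect elsewhere: its chest imaging row is wholly blank although Preoperative investigation requires that examination. Trial status also refers to a full protocol, version 5.0, and sites may work from that and not from the article's table. Both points are fair. They limit what can be said about actual data loss, but they do not remove the contradiction between table and text.

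**Conclusion.** The point holds in two limited parts.

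The schedule conflict is plain on the face of the article: one of 13 post-operative assessments is required by the text and not marked in the table. The count assumes that the quarterly visits run from month 3 to month 36. How many 30-day forms have in fact been missed is unknown.

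The analysis conflict is one of clarity. As written, the plan does not clearly support a claim of significantly better quality of life, because a reader cannot tell whether the scores will be tested between arms. It does not follow that they will not be.

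Quality of life is one of several secondary outcomes. Neither part affects the non-inferiority question on 3-year disease-free survival. Both are worth settling because the correction is cheap and uncollected scores cannot be recovered.

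**What to change.** 1. Reconcile Table 1 with Postoperative investigation for the 30-day questionnaire, check both against the current full protocol, and tell all sites which holds. If the assessment is kept, the cost is one form at a visit that already takes place. Forms already missed since recruitment began in January 2019 stay missing. Report how many there are by centre and arm, and take this into account before choosing a time window that includes month 1.

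2. In Statistical methods, do one of the following:
   - State that quality of life is compared between arms by one pre-specified contrast. An example is a repeated-measures model of one named scale over a named period, adjusted for the baseline score already collected and for the randomisation strata (age group and laparoscopic or robotic approach). Report the other scales and visits descriptively with confidence intervals.
   - Keep the analysis descriptive and remove the significance wording from the abstract's Results, with the Conclusion worded to match.

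The first option costs a paragraph and one model, and limits confirmatory quality-of-life claims to the named contrast. The second costs only wording, but gives up the claim. Either choice should be fixed before anyone sees scores by arm.

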## Abstract

**Background:**

Up to the present time, there has remained a lack of strong evidence as to whether sentinel lymph node biopsy can replace lymphadenectomy for early endometrial cancer. The traditional surgery for endometrial cancer includes pelvic lymphadenectomy and paraaortic lymph node resection, but complications often seriously affect patients’ quality of life. Two randomized controlled trials with large samples have proved that lymphadenectomy does not improve the overall recurrence rate and survival rate of patients. On the contrary, it increases the incidence of complications and even mortality. The current trial is designed to clarify whether sentinel lymph node biopsy can replace lymphadenectomy for early endometrial cancer patients with negative lymph nodes.

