**Conclusion:**

This will prove that the prognosis of sentinel lymph node biopsy alone with indocyanine green combined with near-infrared fluorescence imaging is not inferior to that of sentinel lymph node biopsy plus lymphadenectomy for early stage endometrial cancer with negative nodal assessment intraoperatively. In addition, sentinel lymph node biopsy alone with indocyanine green combined with near-infrared fluorescence imaging results in fewer surgical complications and gives patients better quality of life.

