
### Outcomes

Primary Endpoint3-year disease-free survival (DFS): Time from patient randomization to disease progression/death.Secondary EndpointOverall survival (OS): Time from randomization to death from any cause.Quality of life (QoL): The patient’s quality of life, including the living conditions of patients (EORTC QLQ-C30/CX24).Perioperative clinical dataOperation timeIntraoperative blood lossPelvic lymphocyst/Lymphedema of lower limb/Edema of vulva/ Deep venous thrombosis (DVT)/fever (T ≥ 37.5℃)/Postoperative hospital stay.Sentinel lymph node dataIdentified time of SLNIdentified ratio of SLNIdentified site of SLNNegative predictive value of SLNFalse negative rate of SLN

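### The adverse event summary is worded for treatment-related events in an open-label trial that collects all events; an all-cause summary by arm should be stated (minor)

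*Protocol article*

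**What the plan says.** All references are to the protocol article.

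- **Analysis of adverse events (Statistical methods).** "Descriptive statistical analysis will be used for treatment-related adverse events and quality of life scores". This is the only sentence that names an analysis for adverse events. It does not say who judges relatedness, or by what rule.
- **Toxicity (same section).** "Toxicity will be analyzed based on the treatment received". Toxicity is not defined and no relatedness condition is given. The section also defines a safety population: randomised patients who at least start study treatment.
- **Discrete variables (same section).** "Discrete variables (such as presence/absence of postoperative infection) will be aggregated by frequency/proportion", and "Differences in discrete variables between groups will be assessed by chi square test". Neither sentence mentions attribution.
- **Collection (Table 1 and Postoperative investigation).** The row "Adverse Events (CTCAE V3.0)" is marked at the 30-day visit and at the three-monthly follow-up visits to three years, with no restriction to related events.
- **Named complications (Outcomes).** Pelvic lymphocyst, "Lymphedema of lower limb/Edema of vulva/ Deep venous thrombosis" and fever are listed in their own right, again without an attribution condition.
- **Design and expectation.** The trial is open-label (Trial design and surgical quality assurance). The Abstract's Background says of lymphadenectomy that "it increases the incidence of complications and even mortality". The Abstract's Conclusion anticipates that sentinel biopsy alone "results in fewer surgical complications and gives patients better quality of life".

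**The concern.** The plan collects a broad set of events but commits, in words, to summarising a subset of them. Membership of that subset depends on a judgement. In an open-label surgical trial the person judging will usually know whether lymphadenectomy was done, and the protocol itself states that lymphadenectomy causes complications. The same event could then be called related more readily in Arm B than in Arm A.

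The term is also ambiguous here. Both arms have hysterectomy, salpingo-oophorectomy and sentinel biopsy. Treatment-related could mean related to any study surgery, or related to the randomised component, pelvic lymphadenectomy. Under the second meaning Arm A has almost nothing for an event to be related to, and the filter differs by arm by construction.

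At stake is the general safety comparison. The anticipated conclusion speaks of surgical complications broadly, so events outside the named list could contribute to it.

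**Working it through.** **Step 1. Which events pass through the filter?** No figure in the protocol bears on this, so the check is mainly one of text.

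| Event | Where it appears | Attribution condition? |
|---|---|---|
| Pelvic lymphocyst | Outcomes; pelvic ultrasound in Postoperative investigation | None |
| Lower-limb lymphedema | Outcomes; leg circumference plus ultrasound | None |
| Vulvar edema | Outcomes | None |
| DVT | Outcomes; Doppler when symptomatic | None |
| Fever | Outcomes, with a temperature threshold | None |
| Postoperative infection | Statistical methods, as the example of a discrete variable | None |
| Other CTCAE events, e.g. pain, organ injury, chylous ascites (the last named in the Discussion) | CTCAE collection at each visit | Yes, as the summary sentence is worded |

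Only the last row is exposed. Even there, intraoperative complications are separately recorded (Operative investigation), so some organ injuries may also be captured without attribution. The article does not say how that record is analysed.

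**Step 2. How large could the distortion be?** This is an illustration only. Let p be the true any-cause event risk, equal in both arms, and let aA and aB be the proportions of events called related. The related-event rates are p·aA and p·aB, and the spurious difference is p·(aB − aA). The one input from the protocol is n = 361 per arm (Sample size). The values of p, aA and aB are all assumptions.

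- p = 0.30, aA = 0.6, aB = 0.7: 0.18 vs 0.21, difference 3 points.
- p = 0.30, aA = 0.6, aB = 0.8: 0.18 vs 0.24, difference 6 points.
- p = 0.50, aA = 0.6, aB = 0.8: 0.30 vs 0.40, difference 10 points.

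**Step 3. What if such rates were tested?** The chance of a two-sided p < 0.05 is approximately Φ[(d − 1.96·SE0)/SE1], where d is the difference, SE0 = √[2·p̄(1 − p̄)/n], p̄ is the mean of the two rates, and SE1 = √[(pA(1 − pA) + pB(1 − pB))/n].

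- 0.18 vs 0.21: (0.03 − 1.96 × 0.02949)/0.02947 = −0.94, giving 17%.
- 0.18 vs 0.24: (0.06 − 1.96 × 0.03032)/0.03023 = 0.02, giving 51%.
- 0.30 vs 0.40: (0.10 − 1.96 × 0.03550)/0.03531 = 0.86, giving 81%.

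Other assumptions give other answers. With p = 0.20, attribution of 50% vs 60% gives 10% vs 12% and a 13.5% chance. Attribution of 50% vs 70% gives 10% vs 14% and 38%, and 40% vs 80% gives 8% vs 16% and 91%. With p = 0.10 and 50% vs 60% the rates are 5% vs 6% and the chance is 8.5%. The result is driven almost entirely by the assumed attribution gap, and with no gap it returns to the nominal 5%.

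**The case against.** Several objections have force.

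- **The sentence is not exclusive.** It assigns a method to related events and does not say that others are left out. The toxicity sentence and the safety population carry no relatedness filter. This stands. The answer is only that no other sentence commits to an all-cause summary.
- **The expected benefit rests on other outcomes.** A reader might infer that attribution could by itself produce a finding of fewer complications. The documents do not support that. The Abstract's Results ties the expectation to operation time, lymphocyst, lymphedema and vulvar edema. These are listed outcomes, and lymphocyst and lymphedema have set methods of assessment. Infection, which might look like a natural example of the problem, is handled as an ordinary discrete variable. Unblinded detection of these outcomes would be a different question.
- **The summary is descriptive.** The rejection rates above belong to a test that the adverse event sentence does not plan. This largely stands. The general chi-square sentence, and the sentence on 95% confidence intervals for group differences, do not rule out a formal comparison. A descriptive table of distorted rates can also mislead.
- **Arm-aware attribution is inferred.** The open-label design makes it plausible, but the article does not document who attributes.
- **An independent committee reviews grade 3 and 4 events, serious events and deaths without a stated causality filter.** That is true, but it is monitoring during the trial and does not define the comparative report.
- **This is a condensed article.** The full protocol or an SAP may list all-cause tables. That is possible. The point concerns the wording that the article does fix.

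**Conclusion.** The point holds as a minor one, limited to the general CTCAE summary. The wording selects events by a judgement that may differ by arm, in an open-label trial with no blinded attribution described. That could bias the comparison of events outside the named outcomes. It does not reach lymphocyst, lymphedema, vulvar edema, DVT, fever or postoperative infection.

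The size is unknown. The 3 to 10 point differences and the 17% to 81% rejection rates depend wholly on assumed risks and attribution proportions, and the rejection rates also on a test of a summary that the plan calls descriptive. They show that the mechanism is not negligible if an attribution gap exists. They are not error rates of this trial.

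**What to change.** In Statistical methods, state that all adverse events will be summarised by arm in the safety population regardless of attribution, with treatment-related events in a supplementary table.

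The cost is one sentence and one additional table, since the events are already collected at every visit. The small downside is that background events unrelated to surgery enter both arms and dilute the rates somewhat. The supplementary table of related events keeps that information available.

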### Sample size

The primary endpoint of this study is 3-year DFS. According to the results of previous research, patients with stage I endometrial cancer who received laparoscopy had 3-year DFS of 88.6% [18]. It is assumed that the 3-year DFS of the reference group and the experimental group is 88%, and the non-inferior boundary value is 8%. Considering the 20% loss of follow-up rate, 361 subjects need to be included in each group to ensure 80.0% power using a 2-sided log-rank test with a type I error rate of 0.05 to reject the null hypothesis. The total sample size of this study is 722 and the number of outcome events in each group is 40. The sample size calculation was done using the PASS software (version 11.0).

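### Lymphedema and lymphocyst are followed for three years, but the only comparison named for them is a chi-square on proportions, which ignores unequal follow-up

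*Protocol article*

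**What the plan says.** All references are to the protocol article.

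- **Statistical methods, binary outcomes.** "Discrete variables (such as presence/absence of postoperative infection) will be aggregated by frequency/proportion", and then "Differences in discrete variables between groups will be assessed by chi square test". A 95% confidence interval for the difference between groups is promised in general terms. Treatment-related adverse events are to be described only.
- **Statistical methods, time-to-event outcomes.** "Disease-free survival and overall survival curves will be evaluated using the Kaplan Meier method", with a log-rank comparison. No such method is named for complications.
- **Statistical methods, populations.** Toxicity is analysed by treatment received, and there is "a safe population of all randomized patients who at least start the study treatment".
- **Postoperative investigation.** "The following interviews are planned at 1 month, then every 3 months after surgery for 3 years". That list includes pelvic ultrasound for lymphocyst and, for lymphedema, "The development of lymphedema is investigated and evaluated by measuring the circumference of the legs" combined with ultrasound.
- **Sample size.** "Considering the 20% loss of follow-up rate", 361 patients per group are planned.
- **Outcomes.** Lymphocyst, lower-limb lymphedema, vulvar edema, deep venous thrombosis and fever stand under the perioperative heading, beside operation time, blood loss and hospital stay.
- **Abstract.** Lower incidence of lymphocyst, lymphedema and vulvar edema is an expected result, and fewer surgical complications is part of the anticipated conclusion.

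**The concern.** One visit at 1 month and twelve more at 3-month intervals make up to 13 occasions on which lymphedema or lymphocyst can first be found. A patient last seen at month 3 has had far less chance of a recorded event than one seen for 36 months, yet a presence/absence table gives both the same weight. The article does more than leave the method to an analysis plan: it names one, and that method has no place for follow-up time.

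Fewer complications is the main benefit offered in exchange for accepting non-inferiority on disease-free survival. The trial is open-label and the arms are expected to differ in morbidity, so loss to follow-up may well differ between them. In that case the crude comparison is distorted, in a direction that depends on which arm loses more patients.

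**Working it through.** **Inputs from the document.** 361 per arm, 20% loss, 3 years of follow-up. The 20% is a planning allowance for disease-free survival; I apply it to complications because they are assessed at the same visits.

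**Assumptions.** The document gives no complication rates, so I take true 3-year incidences of 5% v 15%, 10% v 25% and 10% v 16% (Arm A v Arm B). Loss is exponential and independent of the complication. Lost patients stay in the denominator and count as event-free unless an event was seen before loss.

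**The plan's own figure.** None is stated for complications. The sample size that supplies the 20% reproduces roughly:
- Margin hazard ratio: ln(0.80)/ln(0.88) = 1.746.
- Events at one-sided 0.05 and 80% power: 4 × (1.645 + 0.842)² / (ln 1.746)² = 79.7, or 40 per arm as stated.
- With exponential 20% loss over 3 years, the event probability is 0.1078 per patient, so 79.7/2/0.1078 gives 370 per arm, within 3% of 361.

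The stated two-sided 0.05 would need 102 events. That is a separate matter, and nothing below depends on it.

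**Formula.** For true 3-year incidence P and 3-year loss L, put a = −ln(1−P) and b = −ln(1−L). With constant hazards

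crude = a/(a+b) × [1 − (1−P)(1−L)].

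For other onset patterns, crude = ∫ (1−L)^(t/3) dF(t) over 0 to 3 years, where F(t) = 1 − exp(−a(t/3)^k). Here k < 1 means early onset, k = 1 constant hazard and k = 2 late onset.

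**Example at k = 1, L = 20%.** For P = 10%, 0.1054/0.3285 × 0.28 = 9.0%. For P = 25%, 0.2877/0.5108 × 0.40 = 22.5%. The difference is 13.5 points instead of 15.0.

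**Equal 20% loss**

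| Onset | True 5% v 15% (10.0) | True 10% v 25% (15.0) |
|---|---|---|
| Early, k = 0.3 | 4.8 v 14.3, diff. 9.6 | 9.5 v 23.9, diff. 14.4 |
| Constant, k = 1 | 4.5 v 13.5, diff. 9.0 | 9.0 v 22.5, diff. 13.5 |
| Late, k = 2 | 4.3 v 13.0, diff. 8.7 | 8.6 v 21.7, diff. 13.0 |

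Rates and differences shrink by about 4 to 14%. The ceiling is 20%, reached only if every loss came at time zero. The risk ratio is essentially unchanged (3.00 v 3.01 for 5% v 15%). Power at 361 per arm for 5% v 15% falls from 99.5% to between 98.6% and 99.3%.

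**Unequal loss, k = 1**

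| True | Loss A / B | Crude | Difference (true) |
|---|---|---|---|
| 10% v 16% | 15% / 25% | 9.2 v 14.0 | 4.7 (6.0) |
| 10% v 16% | 25% / 15% | 8.7 v 14.8 | 6.1 (6.0) |
| 10% v 25% | 15% / 25% | 9.2 v 21.9 | 12.6 (15.0) |
| 10% v 25% | 30% / 10% | 8.4 v 23.8 | 15.4 (15.0) |
| 10% v 12% | 30% / 10% | 8.4 v 11.4 | 3.0 (2.0) |

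Under unequal loss the risk ratio is no longer protected. For 10% v 16% (true 1.60), 0.140/0.092 gives about 1.51 and 0.148/0.087 about 1.70.

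**Early events.** Expected loss by day 30 is 1 − 0.80^(30/1095.75) = 0.6%, so a chi-square on 30-day events is practically unaffected. For 10% v 16% with k = 0.3, the same integral gives 5.4 points under 15%/25% loss and 6.05 under 25%/15%, much closer to 6.0.

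**Completers only.** With 361 × 0.8 = 289 per arm and loss independent of the complication, the shrinkage above does not arise. Power for 5% v 15% is then 98.1%. Patients seen for part of the 3 years are discarded, and selection becomes a concern if loss is related to morbidity.

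**The case against.** A reader might infer that the plan counts lost patients as event-free and so understates both the rates and the difference. The document does not support that. No section sets the denominator for complications; the safety population of all who start treatment only makes an all-treated denominator plausible. Nor is the direction fixed: the difference can be overstated when Arm A loses more patients.

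Other points against:

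- *Denominator, time window and missing-data rules belong in an analysis plan.* That stands, and their absence from a condensed article is not held against it. What remains is that the article names a test which does not use follow-up time.
- *The Outcomes section treats these complications as perioperative.* It does, and if that meant a 30-day window there would be almost no problem. But no section sets such a window, and lymphocyst and lymphedema are explicitly placed in the 3-year visit schedule. Vulvar edema is not named there, so the point is made for the first two only.
- *The effect is small.* That stands for equal loss. The sharper figures need the assumed unequal-loss patterns, and the 25%/15% overstatement for 10% v 16% is only 0.1 point.
- *Competing-risk methods are a refinement here.* Largely true: with 88% assumed 3-year disease-free survival, deaths should be few. The gain comes from using follow-up time; the allowance for death adds little.

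**Conclusion.** The point holds as a modest, inexpensive improvement. Lymphedema and lymphocyst are ascertained repeatedly over 3 years, loss of about 20% is allowed for, and the only between-group comparison named for binary outcomes ignores unequal follow-up.

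If all treated patients form the denominator, equal 20% loss costs about 4 to 14% of the crude rates and of the absolute difference, with the risk ratio and power nearly intact. That would be unlikely to reverse a conclusion of fewer complications. The better reason to act is unequal loss, whose effect on size and direction cannot be known beforehand: 4.7 or 6.1 points for an assumed true 6.0.

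All sizes rest on assumed complication rates, exponential loss and the inferred denominator. They shrink towards nothing if most events are early.

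**What to change.** In Statistical methods, separate the complications by observation period.

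- **Lymphedema and lymphocyst, and vulvar edema if it is recorded at the same visits:** analyse time from surgery to first recorded occurrence, censored at the last visit at which the complication was assessed, with death as a competing event. Report the 3-year cumulative incidence per arm (Aalen-Johansen), the difference with its 95% confidence interval, and Gray's test.
- **Events complete by the 30-day visit:** keep the chi-square test.
- **Loss to follow-up:** report it by arm beside these results. Cumulative incidence deals with unequal follow-up but still assumes that loss is unrelated to the complication, so a marked imbalance would need a sensitivity analysis.

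The cost is a change of wording and a little more programming. The visit-based assessments are already planned, so no new data are needed. The gain is small if most events turn out to be early.
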